### Sample size {14}

This study will be powered to demonstrate superiority of arm 3 “novel intervention” over arm 2 “best practice” after 1 year. Given the purely incremental nature of arm 3 “novel intervention,” it is assumed it cannot be inferior. Using (i) realistic anticipated outcomes described below with 116% increase in TB case detection rate from 95/100,000/year to 206/100,000/year, (ii) Fokontany as the analysis unit, (iii) intraclass correlation coefficient (ICC) of 0.0005 for sample size adjustment, (iv) average Fokontany cluster size of 1800 inhabitants, and (v) assuming a one-sided *α* = 0.05 test with 80% power, we estimate the number of Fokontany in each arms should be 16 to allow detection of the TB detection rate difference using a simple *t*-test weighed by Fokontany size [23]. TB incidence data from every Fokontany in the Haute Matsiatra region were used to perform sample size calculation. Given the sufficient number of eligible Fokontany in the Vohibato district, 48 Fokontany from this district will be selected to increase feasibility and cluster homogeneity. Multiple simulations were performed to strengthen this sampling size strategy and are presented as Supplementary Materials 1. To estimate anticipated outcomes in each arm, to calculate the ICC and calculate sample size, we used (i) Madagascar TB incidence estimates from WHO, (ii) NTP data disaggregated by primary healthcare facility where services are similar to study interventions, (iii) a comprehensive and systematic baseline survey, and (iv) pilot studies assessing clusters interconnections and impact of arm 1 and arm 2 interventions (see Fig. 2) [11]. Using demographic, distance to healthcare facility, and baseline TB detection rates, the ICC was calculated to be 0.0005. This suggests homogeneity between clusters, which agrees with findings of social network studies performed in the same area and ICC values used in sub-Saharan African studies measuring TB case finding strategies in similar contexts [24]. For arm 1 “standard of care,” anticipated outcomes are adjusted to most reliable, contextualized, and comprehensive primary data from the baseline survey, 75/100,000/year. Using all four sources of preliminary data, we determined realistic anticipated outcomes for arm 2 to be 95/100,000/year and 206/100,000/year for arm 3 [11, 12, 14].

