## Statistical methods

### Statistical methods for primary and secondary outcomes {20a}

First, we will calculate TB case notification rates for each Fokontany. The overlapping TB cases resulting from our RCT study and from NTP report will be counted once in the outcome measures. The primary analysis will compare notification rates between arms after 1 year, using a simple *t*-test and nonparametric Mann–Whitney *U* test weighed by Fokontany size with Fokontany as the unit of analysis. Detection rate differences and 95% confidence intervals (CI) will be reported. The ICC will be calculated from the output of one-way analysis of variance (ANOVA) [27]. As a secondary analysis, the longer-term effect of sustained interventions will be evaluated for 2 years. The longitudinal impact of interventions will be evaluated with a linear mixed-effects model weighed by Fokontany size again conducted at the cluster level. The model will include the yearly TB detection rate, the study arm (1, 2, and 3), the year (first and second), and the interaction arm × year as the fixed effects and Fokontany as the random effect. The least squares mean estimates with 95%CI will be computed from the models. The longitudinal pattern of TB detection rate for each study arm and for each Fokontany will be presented graphically by 6- and 12-month interval. To estimate Fokontany size, we will use two approaches. First, we will consider primary data from the 2019 INSTAT-World Bank census (pilot study) with the 2.7% World Bank estimated annual increase [28, 29]. Then, we will consider the population reported by health authorities upon case finding visits. R software will be used for analyses.

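### The 2-year linear mixed model pools one variance over three arms whose planned rates imply different variances, so its secondary-analysis confidence intervals are modestly off in both directions

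*Protocol article*

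**What the plan says.** The section Statistical methods for primary and secondary outcomes {20a} of the protocol article sets the 2-year analysis: "The longitudinal impact of interventions will be evaluated with a linear mixed-effects model weighed by Fokontany size again conducted at the cluster level". The response is the yearly detection rate. The fixed effects are arm, year and their interaction, and Fokontany is the random effect. The intervals come from this fit: "The least squares mean estimates with 95%CI will be computed from the models". The section names no variance that differs by arm, no robust standard error and no count distribution.

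Outcomes {12} makes the between-arm incidence differences over 2 years secondary outcomes.

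Sample size {14} gives the planning values: a "116% increase in TB case detection rate from 95/100,000/year to 206/100,000/year" for arm 3 against arm 2; for arm 1, "anticipated outcomes are adjusted to most reliable, contextualized, and comprehensive primary data from the baseline survey, 75/100,000/year"; an "intraclass correlation coefficient (ICC) of 0.0005 for sample size adjustment"; and an "average Fokontany cluster size of 1800 inhabitants".

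**The concern.** The variance of a disease rate rises with the rate. At 1800 inhabitants the planned rates mean about 1.35, 1.71 and 3.71 cases per Fokontany-year in arms 1, 2 and 3. A linear model with one random-effect variance and one residual variance averages over arms that differ in this way. Weighting by population corrects for cluster size but not for arm.

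The arm 3 mean, and any contrast that includes arm 3, then gets too small a standard error. The arm 1 and arm 2 means, and the contrast between them, get too large a one. At stake are the intervals for the 2-year differences: those involving arm 3 would look more precise than they are, and the comparison of best practice with standard of care would lose precision.

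**Working it through.** **Inputs (Sample size {14}).** Rates 75, 95 and 206 per 100,000 per year; ICC 0.0005; m = 1800 inhabitants per Fokontany; 16 Fokontany per arm; "assuming a one-sided *α* = 0.05 test with 80% power".

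**1. Reproduce the plan's figure.** Two-proportion formula, 0.00095 against 0.00206, one-sided 0.05, 80% power: 15,081 people per arm. Design effect: 1 + (1800 − 1) × 0.0005 = 1.8995. Clusters: 15,081 × 1.8995 / 1800 = 15.91, which rounds up to 16. This agrees with the statement that "the number of Fokontany in each arms should be 16". The design calculation therefore already ties variance to the rate through p(1 − p).

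**2. One-year variance of a cluster rate.** V = p(1 − p)(1/m + ICC), where 1/1800 + 0.0005 = 0.00105556. In (per 100,000)² units:
- Arm 1: 0.00074944 × 0.00105556 gives 7,911
- Arm 2: 0.00094910 × 0.00105556 gives 10,018
- Arm 3: 0.00205576 × 0.00105556 gives 21,700

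Ratios: 21,700 / 7,911 = 2.7 and 21,700 / 10,018 = 2.2.

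**3. Variance of the two-year mean.** V = p(1 − p)(1/(2m) + ICC), where 1/3600 + 0.0005 = 0.00077778. This gives about 5,829, 7,382 and 15,989. With equal arms and equal cluster sizes the pooled value is the average, 29,200 / 3 = 9,733. It is assumed that the planned rates hold in year 2, since the protocol gives no year-2 rates.

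**4. Model against true standard errors (per 100,000).** The model SE of any difference is √(2 × 9,733 / 16) = 34.9. The true SE is √((Va + Vb) / 16). For a single mean the corresponding figures are √(9,733 / 16) = 24.7 and √(Va / 16).

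| Quantity | Model SE | True SE | Model / true |
|---|---|---|---|
| Arm 3 − arm 2 | 34.9 | 38.2 | 0.91 |
| Arm 3 − arm 1 | 34.9 | 36.9 | 0.94 |
| Arm 2 − arm 1 | 34.9 | 28.7 | 1.21 |
| Arm 1 mean | 24.7 | 19.1 | 1.29 |
| Arm 2 mean | 24.7 | 21.5 | 1.15 |
| Arm 3 mean | 24.7 | 31.6 | 0.78 |

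**5. Coverage by simulation.** The specified model was fitted by REML: size-weighted random intercept, with arm, year and arm × year, and t intervals with 45 df. Each scenario had 8,000 trials with 16 clusters per arm, 2 years, gamma-distributed cluster rates and Poisson counts. The gamma distribution, the pattern of between-cluster variance across arms and the cluster-size CV are assumptions. The range covers constant ICC, constant between-cluster variance and constant CV of rates, each with size CV 0 or 0.4.

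| Two-year quantity | Constant ICC, equal sizes | Range over scenarios |
|---|---|---|
| Arm 3 − arm 2 | 92.8% | 90.3–94.1% |
| Arm 3 − arm 1 | 93.5% | 91.9–94.6% |
| Arm 2 − arm 1 | 98.5% | 96.3–99.1% |
| Arm 3 mean | 87.7% | 82.6–92.2% |

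A separate simulation of the same model at equal sizes gave 92.6%, 93.5%, 98.2% and 86.8%. As a control, equal rates in all arms gave 94.5–95.5%, so the unequal rates cause the departure.

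**The case against.** **The variance structure may be settled in an analysis plan that is not shown.** The protocol nowhere writes that variances are equal, and adding arm-specific variances would not contradict it. This stands in part. But the section lists the fixed effects, the random effect and the weights, and that list as written yields a single pooled variance.

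**The error is small where it matters.** This stands. Every outcome in Outcomes {12} is a difference between arms, and under the protocol's ICC the contrasts with arm 3 lose only about 2 coverage points. The arm 2 minus arm 1 error is conservative. The largest shortfall is in the arm 3 mean, which is reported but is not itself an outcome. If between-cluster variance is the same in all arms, the errors are smaller still.

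**A reader might infer that coverage falls below 80%, or that the trial's conclusion is at risk.** The documents support neither:
- Approximating the model by size-weighted least squares with a size CV of 0.4 gives coverage as low as 79% for the arm 3 mean and 89% for arm 3 minus arm 2. Part of that shortfall comes from the approximation: with all arms at 95 per 100,000 it covers only 93.8% for arm 3 minus arm 2. The model actually specified stays at or above 82.6% and 90.3%.
- Under Interim analyses {21b} the study is declared negative or not on the year-1 result. That t-test compares two arms of 16, for which the pooled standard error is close to correct, because arm 1 does not enter the pool.

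**A reader might also infer that the linear model must give way to a count model.** No coverage is available for such a model with 16 clusters per arm and 1 to 4 cases per cluster-year. It also works on the ratio scale, whereas the outcomes are differences.

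**Conclusion.** The point holds as a modest defect in a secondary analysis. The model as written conflicts with the mean–variance relation built into the protocol's own sample size, and its intervals are off in both directions: somewhat too narrow for contrasts with arm 3, clearly too narrow for the arm 3 mean, and too wide for arm 2 minus arm 1 and for the arm 1 and arm 2 means.

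The standard errors rest only on the planning values, equal cluster sizes, a constant ICC and the assumption that the rates persist into year 2. The coverage figures also need the simulation assumptions, so the scenario ranges should be read alongside the central values. The problem disappears if the arms have equal rates. It therefore distorts the reported precision when an effect exists, and adds little risk of a false-positive result.

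**What to change.** Keep the linear mixed model and the difference scale. State that the random-effect and residual variances are arm-specific, or that cluster-robust standard errors with a small-sample correction are used, with Satterthwaite-type degrees of freedom in either case. A Poisson or negative binomial mixed model of yearly counts with a log-population offset can be added as a sensitivity analysis.

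With arm-specific variances, constant ICC and equal sizes, simulated coverage becomes 95.2% (arm 3 minus 2), 95.0% (3 minus 1), 95.9% (2 minus 1) and 94.3% (arm 3 mean). Across the unequal-rate scenarios it is 94.0–95.6% for arm 3 minus 2 and 94.9–95.9% for arm 2 minus 1.

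The cost is a sentence in the plan, slightly more analysis code and wider arm 3 intervals. There is also a loss: the arm 1 and arm 2 mean intervals move from conservative (98.9% and 97.5%) to slightly below nominal (92.5% and 92.9%). The arm 1 mean ranges over about 90–95% across scenarios, because its counts are very low.

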### Interim analyses {21b}

Interim results will be analyzed every 12 months by the steering committee. If a statistically significant benefit is shown early in the study, results will be disseminated, and the study will be continued until interventions have been implemented for a 2-year period in all clusters to assess longer term impact on TB control (statistical methods for primary and secondary outcomes). If no significant difference between groups is seen after 1 year, this study will be considered negative. We will complete 2 years of intervention to further investigate transmission risk factors emerging from outbreak investigations and long-term impact on case detection rates.

### Methods for additional analyses (e.g., subgroup analyses) {20b}

This study is not powered for sub-group analyses. We will report outcomes stratified (i) by available Fokontany level covariates (baseline TB rate, distance to the closest CDT, Fokontany population in each Fokontany, and closest NTP center) and (ii) by collected demographic variables of TB case participants (sex: female vs male). The exact demographic measures for non-TB case habitants are non-known and will be assumed of (i) equal sex proportions and (ii) 14.4% children < 5 year old age proportion [18]. This analysis will inform on the added value of epidemiologic investigations in women among which TB is frequently under-reported [30, 31].

### Methods in analysis to handle protocol non-adherence and any statistical methods to handle missing data {20c}

The unit of analysis is the Fokontany, and the intervention is at community level. Since we will use administrative quarterly reported data from local CDTs, we do not expect to have missing values for primary outcomes and cluster level covariates. Any inconsistencies for the individual level covariates (sex, age < 5 years) will be investigated with health authorities responsible for data collection. If the values cannot be verified, the simple imputation will be performed. The source of TB case detection for arms 2 and 3 (active case finding or standard of care) will be collected and reported descriptively by each calendar quarter.

### Plans to give access to the full protocol, participant-level data, and statistical code {31c}

The full study protocol and research tools are included in this publication and supplementary materials.

## Oversight and monitoring

### Composition of the coordinating center and trial steering committee {5d}

A trial steering and data safety committee will meet every 12 months and will include the principal investigator (PI), a biostatistician, the head of the local reference laboratory, the head of the in-country institution epidemiology unit, and external experts in TB molecular epidemiology and genomics. Its role will be to review aggregated results and compliance to the protocol as well as to periodically re-evaluate the need to amend study objectives and procedures. A local knowledge translation committee will meet every 6 months and will include regional health officials and community representatives. Its role will be to maintain communication between researchers and the study communities as well as providing feedback on results to local institutions.

### Composition of the trial steering committee, its role and reporting structure {21a}

A trial steering committee will meet weekly and will include the PI, the study coordinator, the data manager, and in-country co-investigators. Its role will be to address routine challenges in study implementation and ensure fluid communication between laboratory and clinical partners. The trial steering committee is independent from the sponsor. The sponsor (CIHR) is a Canadian public funding agency that plays no role in study design, activities, or results reporting.

### Adverse event reporting and harms {22}

This trial strictly involves case finding, diagnosis, and contact tracing. There are no safety or health risks to participants in this study as there is no additional therapeutic intervention or clinical sampling required. TB patients are referred to the NTP for free access to treatment and follow-up.

### Frequency and plans for auditing trial conduct {23}

A weekly audit of data entry will be performed by the local coordinator and local data manager. A trimestral field site audit will be performed by the institution’s clinical trial expert. No external audit will occur.

### Plans for communicating important protocol amendments to relevant parties (e.g., trial participants, ethical committees) {25}

Important modifications to the protocol will be communicated to relevant parties, including the central operational team, the local and Canadian Institutional Review Board (IRB), the NTP, and the trial registries. Local officials, responsible for patients’ treatment and follow-up, will also be notified.

## Dissemination plans {31a}

For all dissemination activities, authorship will follow guidelines of the International Committee of Medical Journal Editors (ICMJE). We aim to publish study results in international scientific conferences and peer-reviewed publications. Results will be presented at the Malagasy Infectious Diseases Society (SPIM) annual conference. Results will be presented to local health officials and community representatives in regional meetings.

## Discussion

This trial aims to prove systematic prospective WGS embedded within TB control programs in high-incidence settings allows to identify transmission chains and leads to additional diagnoses and patients’ notifications. Although several countries or public health agencies have transitioned to systematic WGS for TB (Netherlands, England, New York State), those are low-incidence settings where transmission dynamics are expected to be different and the measured impact on TB control cannot be assumed to be the same in countries like Madagascar.

## Trial status

The trial with protocol version 3.0 (January 28, 2022) was registered on the ClinicalTrials.gov register with the number NCT05406453 on June 10, 2022. Inclusion started on May 16, 2022, and is expected to be completed by the end of September 2025 (see Fig. 3).

**Fig. 3 Fig3:**
[figure not shown]
Schedule of enrolment, interventions, and assessment SPIRIT figure

## Data Availability

The final trial data will be available upon publication of the study result. Additional data will be available upon request to the corresponding author. Researchers are not limited to any contractual agreements that limit data accessibility.

## Abbreviations

CERBM: Comité d’Éthique à la Recherche Biomédicale de Madagascar
cRCT: Cluster randomized controlled trial
DST: Drug susceptibility testing
GCP: Good Clinical Practices
HIV: Human immunodeficiency virus
ICC: Intraclass correlation coefficient
ID: Identifier
IRB: Institutional Review Board
MDR: Multi-drug resistant
NTP: National Tuberculosis Program
PCR: Polymerase chain reaction
PI: Principal investigator
SAS: Statistical analysis system
SNP: Single nucleotide polymorphism
TB: Tuberculosis
WGS: Whole genome sequencing
WHO: World Health Organization
